### 2.8. Intervention groups

#### 2.8.1. Experimental group

A physiotherapist will visit the participants of the EG face-to-face to evaluate their health, deliver the informative booklet, and instruct its use and importance. The booklet titled “Self-care program for caregivers of individuals with ALS” contains guidelines for performing physical activities at home (e.g., stretching, mobility, and strengthening) and information on healthy eating, mental health, and routine management, with a schedule for the weekly organization (Appendix 1).

Participants in EG will be divided into subgroups (three to five per subgroup). Each subgroup will participate in a 6-week self-care education program with weekly synchronous meetings (Burke et al., 2019; de Wit et al., 2019) using Google Meet or WhatsApp. Each meeting will address topics related to the physical and mental health of caregivers, including the importance of care and caregivers, physical activities to be performed at home, routine management, and healthy eating (Figure 1). A physiotherapist, psychologist, and nutritionist will lead the meetings, which will last approximately 40 min plus a maximum of 20 min to discuss whether the participants' expectations were met.

**Figure 1 F1:**
[figure not shown]
Topics to be addressed in weekly meetings.

#### 2.8.2. Control group

A physiotherapist will also visit the participants in the CG to evaluate their health condition, deliver the informative booklet, and instruct them on the importance of reading and using the booklet (Appendix 1). Next, trained researchers will contact the participants via phone calls during the 2nd to 6th week of the intervention to verify their physical and mental health and collect information on completing physical exercises and habits proposed in the booklet. The researcher should record any relevant information. Figure 2 shows the questions for participants. After the intervention period, a new visit will be performed for revaluation.

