**Methods:**

This single-blinded randomized clinical trial will recruit 26 caregivers and randomly allocate them to the experimental (EG = 13) or control group (CG = 13). The EG will receive an informative booklet and participate in a 6-week synchronous telerehabilitation program with a neuropsychologist, nutritionist, and physiotherapist to discuss physical and mental health. The CG will receive an informative booklet on self-care and physical activity and weekly phone calls for 6 weeks to solve questions about the booklet. Outcomes will include the caregiver burden (Zarit scale), quality of life (World Health Organization Quality of Life BREF), pain (McGill Pain Questionnaire), stress (Perceived Stress Scale), and depression (Beck Depression Inventory), which will be evaluated at the baseline after the six-week program and 30 days after the program. Additionally, we will assess daily the nocturnal awakenings, sleep patterns, level of physical activity, and heart rate variability.

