Depressive symptoms will be evaluated using the Beck Depression Inventory (Beck et al., 1961) since the caregiver burden may cause mental changes and increase the risk of depression over the years of caregiving (Gauthier et al., 2007). This widely used tool has demonstrated good reliability and validity and a Cronbach's coefficient alpha of 0.9 (Toledano-Toledano and Contreras-Valdez, 2018). It consists of 21 items evaluating various attitudes and symptoms related to depression [e.g., sadness (“I feel sad or discouraged?”), pessimism (“I feel hopeless about the future”), loss of pleasure, guilt, self-criticism, suicidal thoughts, changes in sleeping and eating patterns, fatigue, and decreased libido]. Each item is scored on a scale of 0 (indicating the absence or minimal presence of the symptom) to 3 (representing severe presence of the symptom), with higher scores indicating a higher level of depression. (Beck et al., 1961).

Nocturnal awakenings

Nocturnal awakenings will be evaluated using the *Sênior Saúde Móvel* platform (Rodrigues et al., 2022), a new wearable device to monitor outcomes related to health, such as nocturia. Nocturia is the need to wake up during sleep to urinate, with each urination preceded and followed by sleep (International Continence Society, 2018). This condition causes significant discomfort and has shown a high prevalence in adults (Vaughan and Bliwise, 2018).

Sleep patterns

Sleep patterns will also be evaluated using the *Sênior Saúde Móvel* platform (Rodrigues et al., 2022). Studies have shown that sleep disturbances are closely related to increased caregiver burden (Leggett et al., 2018; Perez et al., 2022). Moreover, hypervigilance, cohabitation with the individual being cared for, and caregiver tension have been associated with sleep impairments in caregivers. Thus, this platform will allow us to collect comprehensive data on the sleep quality and patterns of caregivers, providing valuable insights into their overall wellbeing.

Level of physical activity

The level of physical activity will be analyzed using the *Sênior Saúde Móvel* platform (Rodrigues et al., 2022) since it predicts physical and psychological stress which can impact caregivers' health (Stults-Kolehmainen and Sinha, 2014).

Heart rate variability

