### 2.12. Adverse events

Adverse events will be self-reported and recorded during the weekly contact with the participant during the intervention (via video or phone call), or at other periods (via message and informative booklet). However, if participants need to report any occurrence, they can contact the researchers at any moment. Potential adverse events will guide adaptations to the exercise program and help the researchers to manage difficulties faced by the caregivers.

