### 2.13. Adherence rate

Adherence to the intervention will be calculated by the percentage of participants who completed the 6-week program. Moreover, adherence strategies (e.g., phone calls) will remind participants of sessions and evaluations, and schedules will be flexible and adjusted according to the needs of participants. Potential issues hampering participation or continuity in the study will be prevented or solved, such as unexplained absence in the interventions, conflicting schedules with the activities of caregivers (e.g., meals and hygiene of the individual with ALS or caregiver), and inadequate environments (e.g., noisy or lacking privacy). These issues will be solved by guiding the caregivers to perform the intervention in a calm environment (i.e., without distractions) and adjust their daily routine to spend time on health improvement and rescheduling the session days or times if needed. Two absences without replacement, illness, disorder, or persistent pain hampering continuity will be considered non-adherence to the program.

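### Adverse events and booklet-exercise completion are ascertained differently in the two arms, and the control contact schedule is described inconsistently

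*Protocol article*

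**What the plan says.** Adverse events (section 2.12): "Adverse events will be self-reported and recorded during the weekly contact with the participant during the intervention (via video or phone call"). The same section adds reporting by message and through the booklet at other times, and lets participants contact the researchers whenever they need to. Reports are to be used to adapt the exercise programme.

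Experimental group (section 2.8.1): caregivers are placed in subgroups of three to five. "Each subgroup will participate in a 6-week self-care education program with weekly synchronous meetings". "A physiotherapist, psychologist, and nutritionist will lead the meetings, which will last approximately 40 min", followed by up to 20 minutes on whether expectations were met.

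Control group (section 2.8.2): "trained researchers will contact the participants via phone calls during the 2nd to 6th week of the intervention". The calls check the caregiver's health and "collect information on completing physical exercises and habits proposed in the booklet"; the questions are listed in Figure 2. The abstract instead describes "weekly phone calls for 6 weeks to solve questions about the booklet". The Discussion describes the asynchronous arm as followed up through messages and the booklet, with no mention of calls.

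Adherence (section 2.13): "Adherence to the intervention will be calculated by the percentage of participants who completed the 6-week program". Two absences that are not made up count as non-adherence. The definition is not split by arm.

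Common measure (section 2.11.2): "The level of physical activity will be analyzed using the" wearable platform, with no restriction to one arm. The abstract says this is assessed daily, and the Discussion names the platform for monitoring adherence.

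**The concern.** How an adverse event is found should not depend on the arm. Here the one active route does: a meeting among peers run by the intervention team in one arm, a researcher's call with set health questions in the other. People may report more, or differently, when asked individually. A difference in event counts could then come from the method of asking rather than from safety. With 13 caregivers per arm, one or two extra reports would change the apparent contrast. Because reports also feed back into the exercise programme, unequal detection could lead to unequal adaptation.

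Exercise completion raises the same issue. Both arms receive the booklet, but the text describes asking about completion only in the control calls. If the trial shows an effect on burden or quality of life, readers will want to know whether the arms differed in how far they followed the booklet.

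Finally, the comparator is described in three ways, so a reader cannot tell how many contacts controls receive, or for what purpose.

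**Working it through.** The document gives no figure for this point, so there is nothing to reproduce first. The check sets the descriptions side by side and then sizes the one part that can be counted.

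**Step 1. Ascertainment by arm**

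| | Experimental (2.8.1) | Control (2.8.2) |
|---|---|---|
| Weekly contact | Group video, 3 to 5 caregivers | Phone call |
| Run by | Physiotherapist, psychologist, nutritionist | Trained researchers |
| Health questions | None stated in the text | Stated, listed in Figure 2 |
| Booklet-exercise completion | None stated in the text | Stated |
| Open reporting at any time (2.12) | Yes | Yes |
| Wearable activity (abstract, 2.11.2) | Yes | Yes |

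The first four rows differ by arm and the last two do not.

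**Step 2. Planned contacts.** Inputs: 13 per group (section 2.3); 6 weekly meetings (2.8.1); calls in weeks 2 to 6 (2.8.2). One call per week is an assumption, since 2.8.2 does not state the frequency.

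- Experimental: 13 × 6 = 78 caregiver-contacts.
- Control, by 2.8.2: 13 × 5 = 65.
- Shortfall: 78 − 65 = 13, and 13/78 = 17%.
- Control, by the abstract: 13 × 6 = 78, no shortfall.

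**Step 3. What one missing contact is worth.** If each contact yields a report with probability p, independently and equally in both arms, the chance of at least one report over k contacts is 1 − (1 − p)^k. The document gives no p, so a range is assumed.

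| p | k = 6 | k = 5 | Difference (points) | × 13 caregivers |
|---|---|---|---|---|
| 0.05 | 26.5% | 22.6% | 3.9 | 0.50 |
| 0.10 | 46.9% | 41.0% | 5.9 | 0.77 |
| 0.20 | 73.8% | 67.2% | 6.6 | 0.85 |
| 0.30 | 88.2% | 83.2% | 5.0 | 0.66 |

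The schedule gap alone is worth about 4 to 7 percentage points, or less than one caregiver in 13. A week-2 call that picks up a week-1 event would shrink it further.

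**Step 4. Direction.** Individual structured questions would tend to raise control reports; one call fewer would tend to lower them. The two pull in opposite directions and the first cannot be sized from the document, so the net direction is unknown.

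**The case against.** The case on the other side is substantial. Section 2.12 sets one approach for both arms, self-report at a weekly contact plus open routes, so an experimental-group caregiver need not speak in front of peers. Activity is measured daily by the same device in both arms, and the Discussion offers that device as the answer to unreliable self-applied exercise. The Discussion also says that caregivers will be asked about difficulties with the exercises, without limiting this to one arm. Figures 1 and 2 are not shown, so the meetings may contain such questions. Adverse events and adherence are not listed outcomes, and no between-arm test of either is announced. The different mode of contact is also largely the intervention itself, and an individual form in the experimental group borrows a little from the control condition.

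Most of this stands, and it limits the point. A reader might infer that adverse events, exercise and adherence cannot be compared between the arms at all. The document does not support that, given the shared routes and the shared device. A reader might also infer that exercise is measured in one arm only; that is true, on the text, only of stated questions about completing the booklet exercises. Nor does adherence have two definitions: it has one, and what an absence or completion means for controls is detail that an article may leave to the full protocol.

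What the objection does not remove is that the active route is stated and differs by arm. General activity from a wearable is not completion of the booklet's exercises and habits. Two arms with different adverse-event totals will be compared by readers, whether or not a test is announced.

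**Conclusion.** The point holds as a modest one. Between-arm comparisons of adverse events and of self-reported booklet-exercise completion are open to ascertainment bias, because the weekly contact at which they are gathered differs in setting, staff and stated questions. The three accounts of control contact contradict one another and must be reconciled.

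The schedule component is small: under one caregiver per arm for assumed report rates of 5% to 30% per contact, and zero if the abstract is right. The 17% shortfall should not be read as a 17% loss of events. It counts contacts, rests on one call per week, and ignores the physiotherapist's visit to controls, whose timing relative to week 1 is not stated. The effect of group against individual questioning is plausible but unquantified.

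A reader might extend the point to burden and quality of life. The document does not support this: section 2.11 has all participants reassessed on the questionnaires by a researcher outside the intervention. No change in sample size follows.

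**What to change.** 1. Ask the same short adverse-event and exercise-completion questions of each caregiver individually, in the same weeks, in both arms: by call in the control group and by a brief individual form in the experimental group.
2. Reconcile the abstract, section 2.8.2 and the Discussion on the number, weeks, mode and purpose of the control contacts.
3. Report completion of the booklet exercises in both arms, and meeting attendance separately for the experimental group.

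Cost: protocol wording, a weekly form of a few questions, and at most 13 extra calls (one for each of 13 controls, if week 1 is added). The downside is that the experimental group gains a brief individual prompt each week. Controls already receive one by phone, so the effect on the contrast should be slight if the form is confined to those questions.

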**Figure 2 F2:**
[figure not shown]
Control questions and recommendations to verify the mental and physical health of participants.

### 2.9. Study procedures

After receiving the informative booklet, participants will respond to questionnaires to characterize the sample and evaluate cognitive function. In the baseline evaluation, the caregiver burden, quality of life, pain, stress, and depression will be evaluated. Next, participants will be randomly assigned to the CG or EG. Outcomes will be revaluated after the 6-week program (revaluation 1) and 30 days after the program (revaluation 2) (Figure 3). If the EG shows better results than CG at the end of the study, the same intervention will be available for CG to ensure equality of treatment for all participants.

**Figure 3 F3:**
[figure not shown]
Flowchart of the study.

### 2.10. Sample characteristics

#### 2.10.1. Sociodemographic, clinical, and anthropometric evaluation

During the delivery of the informative booklet, anthropometric data (i.e., height and weight) will be collected using a measuring tape and portable digital scale. Sex, time spent caring for a patient (in months), time of ALS diagnosis, relationship of the individual with ALS, profession, and age will also be collected. These data will be recorded on the identification form to characterize the sample.

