## 1. Introduction

Caregivers have a low quality of life due to the patient worsening, challenges faced with the progression of the health condition, changes in the routine, and reduction in leisure activities (Diniz et al., 2018; Alves et al., 2019; Nogueira et al., 2019; Sanches Slusarski Martins et al., 2022). Although the low quality of life and increased burden of caregivers are well-established characteristics in literature, this topic still requires greater visibility and attention to propose interventions (Burke et al., 2017; Sandstedt et al., 2018).

Informal caregivers (i.e., unpaid individuals who help patients in activities of daily living and medical programming) may also experience issues in family relationships and economic difficulties and suffer from social stigma and physical burden (Ploeg et al., 2017). Approximately 70 to 80% of caregivers are informal; among these, 30 to 68% have anxiety or depression (Wilz and Kalytta, 2008). In addition, the strain increases the risk of cardiovascular diseases and mortality by 23 and 63%, respectively (Richard and Scott, 1999).

Individuals with amyotrophic lateral sclerosis (ALS) present progressive muscle weakness, fatigue, and reduced mobility and functional activities (Lui and Byl, 2009). Moreover, a multidisciplinary team treats ALS focusing on symptoms (Ferreira et al., 2016) since this disease progression cannot be reversed or changed, requiring intermittent care. Informal caregivers are essential to support this population due to the intensive and complex care required (D'Alvano et al., 2022; Poppe et al., 2022). Schischlevskij et al. (2021) found that the functional status and disease severity of individuals with ALS were the main factors influencing caregiver burden. Moreover, cognitive changes (e.g., impaired attention, focus, and memory) and behavioral changes (e.g., irritability, frustration, impatience, and social isolation) in caregivers of individuals with ALS (Burke et al., 2015; Beeldman et al., 2016) and the need to learn how to manage assisted ventilation and enteral feeding has been involved in caregiver burden (Siciliano et al., 2017; Chu and Oh, 2020).

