### 2.3. Power calculation

Sample size was estimated using an online calculator (Dean, 2007) based on caregiver burden (primary outcome), which was evaluated using the Zarit scale. Moreover, the effect size was calculated based on post-training data from Duran Parra et al. (2019) (mean of 16 ± 9.9 and 31.4 ± 14.9 points for experimental and control groups, respectively), with a mean difference of 15.4 between groups. Thus, 22 participants (11 per group) were estimated, and the total sample was determined as 26 participants (13 per group), considering a dropout rate of 20%.

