### 2.6. Eligibility criteria

#### 2.6.1. Inclusion criteria

Informal caregiver (i.e., family member, friend, or a caregiver without payment) of an individual with ALS (clinically defined, probable, or possible) diagnosed by a neurologist using the (El Escorial Criteria) (Brooks et al., 2000);Informal caregiver of individuals without other neurological diseases associated with ALS (Brooks et al., 2000);Aged 18 years or above;Without cognitive impairment on the Mini-Mental State Examination (MMSE; cutoff point of 25 for literate individuals) to understand the study and the informed consent form Brucki et al. (2003);Literate (at least complete primary education).

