### 2.7. Randomization, allocation, and blinding

Participants will be randomly allocated into the experimental (EG) or control group (CG). A researcher not involved in the intervention will perform the randomization using the www.randomization.com website and maintain the sequence confidential in opaque sealed and numbered envelopes using codes to identify the groups. The content of envelopes will be revealed to the professionals applying the interventions only at the beginning of the program. The researcher responsible for data analysis will be blinded until the end of the study and will not be involved in interventions or data analysis. Professionals, with the exception of the researcher responsible for data analysis, and participants will not be blinded due to the nature of the intervention.

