### 2.14. Statistical analysis

Data will be analyzed using the Statistical Package for the Social Sciences software version 22.0 (IBM Corp., Chicago, IL, USA). Data will be initially characterized using descriptive analysis, and the significance level will be set at 5%. The Shapiro-Wilk test will be applied to verify data normality. Differences between groups on different evaluation periods will be analyzed using linear mixed models. The Bonferroni *post hoc* may be used for statistically significant results to identify specific differences. Moreover, an intention-to-treat analysis will be used to compare the groups by including all participants as allocated after randomization, ensuring an unbiased approach. Participants' data will be analyzed based on their intervention group, regardless of any dropouts. Values from the previous evaluation will be replicated and attributed to missing data due to dropout.

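### Baseline data omit the patient's ALS function and severity, which the protocol reports as the main influences on caregiver burden, so a chance imbalance could be neither seen nor adjusted for

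*Protocol article*

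**What the plan says.** The Introduction of the protocol article reports that a cited study "found that the functional status and disease severity of individuals with ALS were the main factors influencing caregiver burden". It also names having to learn ventilation support and enteral feeding as contributors, and remarks that efficacy at different stages of the disease has been little studied. Burden on the Zarit scale is the outcome used for sample size in section 2.3.

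The baseline data are itemised. Section 2.10.1 lists height and weight, then "Sex, time spent caring for a patient (in months), time of ALS diagnosis, relationship of the individual with ALS, profession, and age". Their purpose is descriptive: "These data will be recorded on the identification form to characterize the sample". Section 2.10.2 adds physical activity, months of caring for any patient, and whether the care is for the same person. Section 2.10.3 adds the caregiver's own MMSE. No item measures the patient's function, severity, ventilation or feeding.

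Section 2.6.1 admits caregivers of "an individual with ALS (clinically defined, probable, or possible) diagnosed by a neurologist" and sets no functional limit. Section 2.7 names no prognostic factor for allocation. Section 2.9 places the burden measurement before randomisation: "In the baseline evaluation, the caregiver burden, quality of life, pain, stress, and depression will be evaluated". Section 2.14 states: "Differences between groups on different evaluation periods will be analyzed using linear mixed models". It names no covariate, and it carries the previous value forward after dropout.

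**The concern.** The factor that the protocol itself puts first in explaining its primary outcome is absent from an otherwise detailed list of data. An analysis plan can add covariates later, but it cannot adjust for a variable that nobody collected, and a baseline table cannot show it by arm. In a trial of 26 people, moderate chance differences in such a factor are common. If one occurred, readers could not tell, and the estimate in that particular trial would be displaced by an unknown amount. The trial also could not describe its own sample by disease stage, although its Introduction regards stage as a gap in earlier work.

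There is a related gap at follow-up. The Zarit items ask about care of a particular person, and outcomes run for 6 weeks plus 30 days in a progressive disease. No item stated for the revaluations records whether the patient is alive and still cared for by the participant. A Zarit value collected, or carried forward under section 2.14, after caregiving has ended could not be reliably picked out.

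**Working it through.** **Inputs from section 2.3:** Zarit "mean of 16 ± 9.9 and 31.4 ± 14.9 points for experimental and control groups, respectively"; difference 15.4; 11 per group evaluable, 13 per group recruited. **Assumed, not in the documents:** severity-burden correlation r = 0.3 to 0.6, the same at each visit; pre-post Zarit correlation ρ = 0.5 to 0.8; a severity effect that is stable over time.

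**1. The plan's own figure.** Pooled SD = √((9.9² + 14.9²)/2) = √160.01 = 12.65. With two-sided 5% and 80% power (power is not stated; 80% is assumed), n = 2 × (1.96 + 0.84)² × 160.01 / 15.4² ≈ 10.6, so 11 per group. The stated figure is reproduced.

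**2. How often an imbalance arises.** The arm difference in a standardised covariate has SD √(2/13) = 0.392. P(|difference| > 0.5) = P(|z| > 0.5/0.392 = 1.275) = 0.20. With 11 per arm the SD is √(2/11) = 0.426 and the probability is 0.24. Both are two-sided, so about 10% of trials with 13 per arm would have an imbalance of this size in the programme's favour.

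**3. Effect of a 0.5 SD imbalance on the Zarit contrast.**

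| Analysis | Formula | Low | High |
|---|---|---|---|
| Post-programme scores, unadjusted | 0.5 × r × 12.65 | 1.9 (r = 0.3) | 3.8 (r = 0.6) |
| Baseline Zarit as covariate | 0.5 × r × (1 − ρ) × 12.65 | 0.4 (r = 0.3, ρ = 0.8) | 1.9 (r = 0.6, ρ = 0.5) |
| Change from baseline | the severity term cancels | about 0 | about 0 |

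Against 15.4 points, the first row is 12 to 25% and the second 2 to 12%.

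**4. Type I error.** Trials with no true effect and 13 per arm were simulated, 40,000 for each pairing of r = 0.3, 0.5, 0.7 with ρ = 0.5, 0.7, 0.8. Over all randomisations, type I error was 4.7 to 5.2% in every analysis. Among trials with an imbalance of at least 0.5 SD (so larger than 0.5 on average):

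| Analysis | Type I error | Mean shift, points |
|---|---|---|
| Post-programme only | 6.7 to 16.0% | 2.7 to 6.2 |
| Baseline Zarit as covariate | 5.2 to 8.6% | 0.5 to 3.0 |
| Change from baseline | 4.6 to 5.3% | at most 0.1 |
| Baseline Zarit and severity | 4.6 to 5.4% | at most 0.13 |

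**5. Precision beyond baseline Zarit.** Adding severity removes a share r²(1 − ρ)/((1 − r²)(1 + ρ)) of the residual variance.
- For r = 0.6, ρ = 0.5: 0.18/0.96 = 18.8%.
- For r = 0.3, ρ = 0.8: 0.018/1.638 = 1.1%.

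Going from one covariate to two with N = 26 costs a variance factor of about 22/21 = 1.048. The net variance ratio therefore runs from 0.812 × 1.048 = 0.85 (a gain of about 15%) to 0.989 × 1.048 = 1.04 (a slight loss).

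**The case against.** A reader might infer that a severity imbalance could pass for a programme effect. The documents do not support that. Randomisation makes chance imbalance in any covariate, measured or not, part of the standard error, and step 4 shows overall type I error staying near 5%. Nor does an imbalance of the size examined come near 15.4 points by itself. The largest shifts also belong to an analysis of post-programme scores alone. The protocol measures Zarit before randomisation and plans a mixed model over the evaluation periods, which removes much or all of a stable severity effect, depending on how the model uses baseline. This part of the objection stands and limits the point.

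It can also be said that covariates and follow-up status fields usually belong in an analysis plan or case report form, neither of which is shown, and that stratifying 26 people is optional. That is fair: the silence of section 2.14 on covariates is no finding, and neither is simple allocation. It does not answer the omission from an itemised list of data.

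Finally, recruitment is from a hospital neuromuscular clinic (section 2.2), so some function data may be recoverable from records, and weekly contacts in both arms might bring a change in caregiving to light. Neither is planned for this purpose, and neither ensures a comparable value at baseline or at each revaluation.

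**Conclusion.** The point holds as a cheap improvement in description, adjustment and precision, not as a defect in validity. The protocol reports function and severity as main influences on its primary outcome and lists only weak proxies for them. About one such trial in five would have an imbalance above 0.5 SD that could be neither seen nor adjusted for. The displacement from a 0.5 SD imbalance is about 0.4 to 1.9 Zarit points with baseline Zarit in the model, up to 3.8 without it, and about 0 for change from baseline. These sizes rest on the assumed correlations and on a stable severity effect. Different rates of decline between arms would escape the baseline score, but the documents give no figure with which to size that.

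Three further inferences go beyond the text. The Introduction speaks of factors influencing burden, not of its change over the follow-up period. The category of possible ALS in section 2.6.1 is diagnostic certainty, not disease stage. No death rate is given, so the number of caregivers bereaved during follow-up cannot be stated.

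**What to change.** - Add to section 2.10.1 the patient's ALS functional score and whether ventilation or enteral feeding is in use, taken at the baseline visit already planned, and report them by arm.
- Pre-specify baseline Zarit as a covariate in the burden model, with the functional score as one further covariate or as a sensitivity analysis.
- At each revaluation, record whether the patient is alive and still cared for by the participant. Zarit values collected or carried forward after caregiving ends can then be identified and examined in a sensitivity analysis, leaving the intention-to-treat analysis in place. Withholding the Zarit from such participants, or restricting the main analysis to the time of caregiving, would condition on an event after randomisation and is not proposed here.

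Stratification is not required. The cost is a few minutes per participant and one degree of freedom for the added score; the precision gain beyond baseline Zarit may be small or absent (step 5 of the working). The items should be settled before enrolment, because baseline severity is hard to recover reliably afterwards. The stated sample size does not change.
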